**Fig. 2 Fig2:**
[figure not shown]
Flow chart of participants throughout the factorial trial of the optimization phase

*Sample size calculation*: The study is powered to detect at least a medium effect size measured by partial eta squared (*ƞ*^2^) = 0.06; the effect size measure for factorial ANOVA [34]. In G* Power 3.0.10 [35], we specified *f*= 0. 0.2526456 based on the required *ƞ*^2^, alpha error= 5% and study power= 80%. For the 8 conditions in Table 2, we used numerator df= (2 levels in MI- 1) X (2 levels in OHPM- 1) X (2 levels in ST videos- 1) = 1 X 1 X 1= 1. A total sample size of 126 will allow the estimation of main effects and interactions using linear regression analysis. This will be rounded to 160 corresponding to 20 parents in each of the 8 experimental conditions.

*Randomization and allocation concealment*: Parents will be assessed for eligibility and randomly allocated by the Ralloc Stata Software [36] to the 8 experimental conditions (Table 2) using a permuted block of size 16, to be able to balance the sample size across the randomization groups. Each block will be a list of 8 randomly ordered conditions, and participants will be randomized to the condition listed in the permuted block. Once all allocations in a block have been used, the next permuted block will be utilized. The randomization schedule will be kept in opaque, sealed envelopes, and the envelopes will be arranged sequentially by a dental assistant who will not be involved in the study. Each envelope will be opened after completing the child’s oral examination at baseline and the experimental condition to which the parent is allocated will be administered. Parents’ enrollment, random sequence generation, and allocation to experimental conditions will be done by an independent researcher (RY) who will be different from the researcher implementing the experimental conditions and assessing the outcomes. The researcher also clinically assessing plaque accumulation (primary outcome) (NA) and the researchers involved in data analysis (MI, MT) will be blinded to the assignment to interventions. At the end of the 6-month period of the study, all children in need of any dental treatment will be referred to a pedodontist in the outpatient clinic. Participants who will be lost to follow-up or who choose to withdraw from the study will be noted and their reasons for doing so as well as the group to which they were allocated will be recorded and reported in the study results*.* All attempts will be made to collect data for the study outcome measures for participants who discontinue or deviate from the interventions.

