### Ethics approval and consent to participate

The study received approval from the Ethics Committee of the Faculty of Dentistry, Alexandria University. IRB No: 00010556-IORG: 0008839. A signed informed consent will be obtained by the principal investigator (MI) from each parent. The informed consent that will be signed by the parents will encompass the data to be collected and its intended analysis and use for the study purpose. No additional studies are planned, and no biological samples are to be collected because of the focus of the study on parents’ behavior and its impact on plaque accumulation in children. The voluntary nature of the study will also be emphasized in the consent form, and the parents will be informed of their right to withdraw from the trial anytime, without incurring any penalties. In addition, no advice will be given to the participants to avoid receiving or seeking any health education content.

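### The researcher who enrols and allocates parents also generates the random sequence, and no stated safeguard keeps upcoming conditions from that person

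*Protocol article*

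**What the plan says.** The paragraph on randomization and allocation concealment (Optimization phase, Factorial trial design) gives three tasks to one person. It says that enrolment of parents, "random sequence generation, and allocation to experimental conditions will be done by an independent researcher". The only separation it claims is that this researcher is someone "who will be different from the researcher implementing the experimental conditions and assessing the outcomes".

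The concealment measures are these:
- "The randomization schedule will be kept in opaque, sealed envelopes".
- "the envelopes will be arranged sequentially by a dental assistant who will not be involved in the study".
- Each envelope is opened once the child's baseline examination is complete.

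The same paragraph describes the blocks twice: "using a permuted block of size 16", and then "Each block will be a list of 8 randomly ordered conditions".

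Under Ethics approval and consent to participate, "A signed informed consent will be obtained by the principal investigator (MI) from each parent". The description of motivational interviewing under Identifying candidate components attaches the same initials to the single researcher who gives the sessions.

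**The concern.** Allocation concealment means that whoever decides on a parent's entry cannot know the next condition. Here the decision and the list lie with the same person. A recruiter who knows what comes next can, deliberately or not, invite, defer or discourage a parent accordingly.

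This trial offers an obvious route for that. Motivational interviewing requires a clinic session of 30 to 45 minutes plus follow-up calls, and the section on the optimization objective names the parent's willingness to spend time as the key constraint. Parents with more time or motivation may well brush more whatever they are assigned. The adjusted regression includes baseline brushing and demographic variables, but no measure of motivation or available time, so it cannot be relied on to remove such selection. Blinded plaque scoring acts only after selection has happened.

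The stakes are direct. Each component is kept or dropped according to whether its main effect reaches a moderate size, so selection on one factor would feed into the composition of the optimized intervention. No auditing is planned, and no body outside the study team monitors the data.

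**Working it through.** **1. Does any stated measure hide the order from the person who generated it?**

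| Measure in the protocol | From whom it hides the order | Does it bind the enrolling researcher? |
|---|---|---|
| Opaque, sealed envelopes | People who have not seen the list | No, that researcher generated it |
| Sequential arrangement by an uninvolved assistant | Nobody further; the order is unchanged | No |
| Opening after the baseline examination | The examiner, until baseline plaque is scored | No, the decision to enrol comes earlier |
| Separation from delivery and outcome assessment | Does not concern the list | No, it limits motive, not knowledge |

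None of the four separates sequence generation from enrolment. Up to 100% of upcoming conditions are knowable to the recruiter, whatever the block size.

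**2. What could a consent-taker who delivers the counselling guess?**

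Assume that this person knows every earlier motivational interviewing (MI) allocation, the block size and the block boundaries, and always guesses the level with more places left. In a block of 2b places, b of them with MI, the expected number of correct guesses is

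E = b + 2^(2b−1) / C(2b, b) − 1/2.

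- Block of 8 (b = 4): 4 + 128/70 − 0.5 = 5.33, and 5.33/8 = 66.6%.
- Block of 16 (b = 8): 8 + 32768/12870 − 0.5 = 10.05, and 10.05/16 = 62.8%.
- Chance: 50%.

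These are upper bounds for one of the three factors.

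**3. Does the total settle the block size?**

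The protocol plans 160 parents, 20 in each of 8 conditions.
- Blocks of 16, each condition twice: 160/16 = 10 blocks, 10 × 2 = 20 per condition.
- Blocks of 8, each condition once: 160/8 = 20 blocks, 20 × 1 = 20 per condition.

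Both schemes reproduce the planned numbers, so the total does not decide between them. They differ in predictability. For someone who knows all past conditions and the block size, the best-guess hit rate over the eight conditions is (1 + 1/2 + … + 1/8)/8 = 34.0% with blocks of 8 and 29.6% with blocks of 16 (the latter from 40,000 simulated blocks), against 1/8 = 12.5% by chance. The share of allocations fully determined by earlier ones is 12.5% and 6.7% respectively.

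**4. Sample size.** With f = √(0.06/0.94) = 0.2526, one numerator degree of freedom, 8 groups and alpha 5%, the stated 126 is reproduced (power 0.803); at 160 the power is 0.888. This point changes neither figure.

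**The case against.** The strongest reply is that foreknowledge is possible but not shown. The article nowhere says that the enrolling researcher keeps or consults the list, and custody of the list may be described in the full protocol, which the article says is supplied as a supplement and which is not at hand. This researcher neither delivers conditions nor scores outcomes, so has less reason to steer. Most entry criteria can be checked: age, plaque, literacy and phone, behaviour rating. If another person takes every consent, the enrolling researcher does not control entry alone. All of this stands as mitigation. It narrows the room for selection but does not restore concealment, because the overlap of roles is an explicit assignment in the text and not an omitted detail.

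On consent, the identity of consent-taker and counsellor is an inference from initials, and those initials are also the abbreviation for motivational interviewing. The randomization paragraph further lists the same initials among analysts blinded to assignment, which would not fit someone who gives the sessions. The inference is plausible but the sponsor has to confirm it.

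On the blocks, a reader might infer that the sequence cannot be produced as described. The documents do not support that. The second sentence may simply name the 8 distinct conditions, each appearing twice in a block of 16, and either scheme is workable. What remains is an ambiguity of wording.

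**Conclusion.** The point holds in a limited form. As written, the plan leaves the recruiter able to know upcoming conditions, and nothing stated prevents it. This rests on the protocol's own allocation of tasks and on no outside assumption.

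A reader might go further and conclude that the envelopes conceal nothing, or that recruitment will be steered. The text supports neither. The envelopes can still hide the order from others, including the consent-taker, and 100% is what the recruiter could know, not evidence of use. Nor do the 63% and 67% measure bias. They depend on the consent-taker being the counsellor, on tracked block boundaries and on optimal guessing, and no effect on the plaque outcome has been derived from them.

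The role overlap should be removed before the first parent is enrolled, because selection at entry cannot be repaired in the analysis. The 16-versus-8 wording is a minor inconsistency.

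**What to change.** - **Separate generation from enrolment.** A team member or other person with no contact with parents before allocation runs the ralloc program and fills and seals the envelopes. The enrolling researcher never receives the list.
- **Preferably separate consent from counselling.** Consent is obtained by someone who does not deliver the motivational interviewing. If the consent-taker and the counsellor are already different people, saying so is enough.
- **Minor: reconcile the block description.** State either 16 with each condition twice or 8 with each condition once, and withhold block boundaries and upcoming allocations from recruiters. Asking that a fixed size printed in a public protocol be kept unknown would defeat itself, so the protection has to come from who holds the list and who sees past allocations.

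A recruiter who still opens the envelopes, and so learns past conditions, would then be limited to the best-guess rates of 29.6% or 34.0% over the eight conditions, instead of possible knowledge of all of them.

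The cost is a reassignment of roles, a text correction and possibly a notification to the ethics committee, since the consent arrangement appears in the ethics section. No additional parents are needed.

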##### b. Selecting the most efficacious components fitting the optimization objective

The combination of components making up the optimized intervention will be selected according to the following procedure [37]:
The three components are labeled *A* to *C*.The main effect of component A will be defined as the difference between the yes level and the no level of that component, averaged across all the levels of components *B*–*C.* This will be calculated by subtracting the mean response in conditions 1–4 in Table 2 from the mean response in conditions 5–8.A two-way interaction involving components *A* and *B* will occur if the effect of *A* at the “Yes” level of *B* is different from the effect of *A* at the “No” level of *B*, averaged across all the levels of *C* and *D.*Regression coefficient estimates will be produced by conducting a factorial ANOVA using effect coding (−1,1).If a component has a main effect with at least a moderate effect size, the “yes” level will be chosen for inclusion in the intervention. If the component does not achieve a moderate effect size or has an effect in the wrong direction, such as increasing the plaque index, the “no” level will be selected. This allows the inclusion of efficacious components and the elimination of components which have no use.An initially selected component may be deselected if it interacts with another component which undermines its effect, or a component not initially selected may be selected if it interacts with another component to enhance its effect.The combination of components which fits within the constraint of the optimization objective will be selected for inclusion in the optimized intervention package.

### Data management and statistical analysis

IBM SPSS Statistics for Windows (Version 25.0. Armonk, NY: IBM Corp) [38] will be used for data analysis. A linear regression model will be used to assess the effect of the components on percent reduction in plaque index score adjusting for the following confounders: parent’s sex, age, education, occupation, brushing using fluoridated toothpaste, number of children in the family, child’s age, and sex. The percent reduction in plaque index scores will be assessed for the subgroups included in the adjusted analysis. All participants randomized into the 8 conditions will be included in the analysis following an intention to treat analysis including those receiving a co-intervention, those with contaminated intervention, and those who do not receive the interventions in the oral health promotion messages and the story telling videos. For participants who drop from the study and have no outcome measures data, multiple imputation will be used to derive the missing data values. Significance will be set at the 5% level.

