#### II. Optimization phase

##### a. Factorial trial design

A factorial trial will be used to compare the levels of the three intervention components: MI, OHPM, and ST videos with the features identified during the preparation phase. Factorial designs are preferred for comparing the three components for two reasons. Firstly, factorial experiments separate component effects, enabling the estimation of the main effect and interactions between components. Secondly, factorial trials are efficient compared to alternative designs because they require fewer participants to achieve the same statistical power. Conducting three individual trials will require three times as many participants as the factorial trial.

*Study setting*: Outpatient clinics of the Department of Pediatric Dentistry and Dental Public Health, Faculty of Dentistry, Alexandria University, Alexandria, Egypt. This outpatient clinic is part of the largest public hospital in the city and is affiliated with Alexandria University. It receives hundreds of patients daily and is a suitable setting for patient recruitment.

*Eligibility criteria*: The inclusion and exclusion criteria are the same as those of the feasibility pilot study.

*Intervention components*: Each of the three components (MI, OHPM, and ST) has two levels: yes (the intervention is applied) and no (the intervention is not applied) as shown in Table 2. Participants will be divided into subgroups, each receiving one of the eight experimental conditions.

**Table 2 Tab2:** Factorial trial design in the optimization phase with 8 experimental conditions

Experimental condition	MI	OHPM	ST
1	No	No	No
2	No	No	Yes
3	No	Yes	No
4	No	Yes	Yes
5	Yes	No	No
6	Yes	No	Yes
7	Yes	Yes	No
8	Yes	Yes	Yes

*Outcome measures*: The outcome assessment uses validated methods and assessment tools including a clinical examination and a questionnaire. Therefore, these tools and methods will not be further assessed in the pilot feasibility study.

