1. Primary outcome: Reduction in the dental plaque index scores of children of participating parents after 3 and 6 months [31] will be measured using the modified plaque index (PlI) of Silness and Löe [32] by another researcher than the one providing the intervention (NA). The World Health Organization (WHO) community periodontal index of treatment needs (CPITN) probe and a disposable dental mirror will be used to assess plaque on 6 index teeth (upper right 2nd primary molar, upper primary right lateral incisor, upper left 1st primary molar, lower left 2nd primary molar, lower left primary lateral incisor, and lower right 1st primary molar) at baseline and after 3 and 6 months. The four surfaces of each tooth will be scored from 0 to 3 and the scores will be averaged per tooth. The scores of the six teeth will be averaged to obtain the mean PlI of the child. The outcome measure is the percent reduction in dental plaque scores calculated as: [(plaque score after 3 or 6 months − plaque score at baseline)/ plaque score at baseline] × 100. The primary outcome measure is reduction in plaque index scores after 6 months.

2. Secondary outcome: Parent-reported frequency of brushing the child’s teeth using fluoridated toothpaste will be assessed by the Arabic version of the WHO questionnaire [33] at baseline, after 3, and 6 months. The questionnaire assesses the frequency of toothbrushing on a 7-point scale ranging from never to twice or more a day. The outcome measure is the change in frequency from baseline to 3 or 6 months categorized as increased (changing from lower to higher frequency), remained the same (reporting the same frequency) and decreased (changing from higher to lower frequency). (Appendix 2)

3. Moderators such as child’s age and sex, the number of children in the family, parents’ age, oral hygiene practices, and education level will be assessed by the questionnaire.

*Participant timeline*: Participant timeline is shown in Fig. 2.

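### The primary analysis models percent change in plaque without baseline plaque as a covariate, while eligibility allows very low or zero baseline scores; the cost in power is conditional, and the outcome can be undefined.

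*Protocol article*

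**What the plan says.** **Outcome.** Under Outcome measures (II. Optimization phase, a. Factorial trial design) the protocol article says "The outcome measure is the percent reduction in dental plaque scores calculated as" the follow-up score minus the baseline score, over the baseline score; the formula ends "plaque score at baseline)/ plaque score at baseline] × 100". The primary time point is fixed: "The primary outcome measure is reduction in plaque index scores after 6 months".

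**Score.** PlI is the mean over six index teeth, each with four surfaces scored 0 to 3. The list begins "upper right 2nd primary molar, upper primary right lateral incisor, upper left 1st primary molar, lower left 2nd primary molar" and continues with a lower left lateral incisor and a lower right first molar. The upper right lateral incisor is the only upper front tooth among the six.

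**Model.** Data management and statistical analysis says "A linear regression model will be used to assess the effect of the components on percent reduction in plaque index score adjusting for" these covariates: "parent’s sex, age, education, occupation, brushing using fluoridated toothpaste, number of children in the family, child’s age, and sex". Baseline PlI is not among them. The component-selection section says "Regression coefficient estimates will be produced by conducting a factorial ANOVA using effect coding" and names no baseline term either.

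**Eligibility.** The pilot criteria admit a child either with plaque index scores of at least 2 or with plaque visible on the upper front teeth. For the factorial trial, "The inclusion and exclusion criteria are the same as those of the feasibility pilot study".

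**Missing outcomes.** All randomised participants are to be analysed. Multiple imputation is planned for participants who drop out and have no outcome data.

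**The concern.** A ratio to baseline does not in general remove dependence on baseline, and it magnifies noise when the divisor is small. Here the divisor has no floor, because the second entry route does not refer to the index-tooth mean. This could have three consequences:

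- A child with zero baseline PlI has no defined outcome, and the stated imputation does not reach a child who was fully followed.
- A few children with low baselines could dominate a component's mean. The component-selection section keeps or drops a component according to whether its main effect reaches a moderate size, so the trial's decision could turn on those children.
- The analysis could have less power than the same data would give with 6-month PlI adjusted for baseline.

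**Working it through.** **1. The plan's own figure.** Inputs from the sample size paragraph: partial eta squared 0.06, alpha 5%, power 80%, numerator df 1, 8 groups.
- f = √(0.06/0.94) = 0.2526, as stated.
- Noncentral F with df 1 and N − 8, λ = N·f²: N = 126 gives power 0.803 and N = 160 gives 0.888.

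The stated 126 is reproduced.

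**2. How low the divisor can go.** PlI is the mean of 6 × 4 = 24 surface scores, so one point on one surface is 1/24 = 0.042.
- Upper right lateral incisor scored 2 on all four surfaces, all else 0: 8/24 = 0.33. At the maximum score of 3: 12/24 = 0.5.
- One surface scored 2: 2/24 = 0.083.
- Plaque only on upper front teeth outside the index set: 0/24 = 0, and percent change is undefined.

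**3. Leverage.** One surface changing by one point moves the outcome by:
- 0.0417/2.0 = 2.1% at baseline 2.0
- 0.0417/0.333 = 12.5% at baseline 0.33
- 0.0417/0.0833 = 50% at baseline 0.083

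Each main effect compares 80 with 80 children. A child going from 1/24 to 12/24 scores (12 − 1)/1 = +1100%, which alone shifts a mean of 80 by 1100/80 = 13.75 percentage points. Going from 2/24 to 12/24 is +500%, a shift of 500/80 = 6.25 points.

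**4. Power, additive effect.** The documents give no baseline distribution, SD or baseline–follow-up correlation (ρ), so these are assumptions. The 2×2×2 trial was simulated at N = 160 (1,000–1,500 runs per scenario), with the effect sized at about f = 0.2526 for the baseline-adjusted 6-month score. Each cell shows percent change without baseline vs 6-month PlI adjusted for baseline:

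| Assumed baselines | ρ = 0.3 | ρ = 0.5 | ρ = 0.7 |
|---|---|---|---|
| all ≥ 2 | 0.84 vs 0.89 | 0.87 vs 0.89 | 0.87 vs 0.87 |
| 0.5 to 3 | 0.75 vs 0.89 | 0.80 vs 0.88 | 0.86 vs 0.88 |
| down to 0.04 | 0.45 vs 0.88 | 0.54 vs 0.89 | 0.62 vs 0.87 |
| including 0 | 0.35 vs 0.88 | 0.45 vs 0.87 | 0.57 vs 0.88 |

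In the last row about one child per trial had no defined outcome. Adding baseline as a covariate while keeping percent change recovers little when baselines run near zero (0.54 to 0.58 at ρ = 0.5).

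A second set of additive runs used baseline mean 1.3–2.0 and SD 0.35–0.5, with the effect sized for about 80% power in the adjusted analysis. Percent change reached 0.40–0.77 against 0.76–0.81. At mean 2.0 and SD 0.35 the loss was 1–10 points.

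**5. Power, strictly proportional effect.** Here the 6-month score is baseline times a factor that carries both the effect and the noise. Cells are percent change vs adjusted 6-month PlI:

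| Assumed baselines | no scoring error | scoring error SD 0.25 |
|---|---|---|
| 2 to 3 | 0.88 vs 0.87 | 0.81 vs 0.83 |
| 0.5 to 3 | 0.89 vs 0.86 | 0.55 vs 0.70 |
| 0.04 to 3 | 0.89 vs 0.83 | 0.16 vs 0.57 |

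With a smaller scoring error (SD 0.1), five of six scenarios with mean 1.3–2.0 differed by under 2 points. Only mean 1.3 with SD 0.5 clearly favoured the adjusted score (0.66 vs 0.78).

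**The case against.** The strongest defence is that plaque may fall in proportion to where it started. Percent change is then the natural scale, and without scoring error it is level or slightly ahead. This stands, so it would be wrong to infer that the baseline-adjusted score is always more powerful. The ranking turns on the shape of the effect and on scoring error, and the plan states neither.

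The size of any loss also rests on assumed inputs. A PlI of at least 2 is one of the two entry routes; if nearly all children enter that way, the loss is small. This stands too.

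A reader might infer that the sample size is wrong. It is not: it is stated as a standardised effect and reproduces exactly. The power comparison is between two ways of using the same data. A reader might also infer that leaving baseline out biases the component effects. Allocation is randomised, so the omission does not in itself bias the comparison.

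Finally, the article says that the full protocol is a supplement, which is not shown here, and a rule for zero divisors could be there. The absence of such a rule should therefore not carry the point. The omitted baseline term is different, because the article itself lists the adjustment covariates.

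**Conclusion.** The point holds as one of efficiency and robustness, and the plan should be changed. Three facts are certain from the article: the outcome divides by baseline PlI, the stated covariates omit baseline PlI, and the entry criteria set no floor on the index-tooth mean. A very low divisor is therefore possible. So is a zero divisor, which leaves the outcome undefined and which the stated imputation does not cover.

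The size of the power cost is conditional. It is about 0–10 points if baselines lie mostly around or above 2, and roughly 20–50 points if low baselines are common and the effect is additive. It is nil under a strictly proportional effect without scoring error; with material scoring error the baseline-adjusted score is better. These ranges rest on assumed correlations of 0.3–0.7 and assumed baseline distributions.

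It would go too far to say that children will drop out of the analysis for this reason. A zero baseline needs plaque on non-index upper front teeth and a score of 0 on all 24 index surfaces, and the documents give no frequency for that.

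**What to change.** Make 6-month PlI the primary analysis variable in one effect-coded linear model containing the three components, their interactions, baseline PlI and the covariates already listed. Use that same model for the component-selection step and for the main analysis. Every child with a 6-month score then has a defined outcome, including any with a zero baseline.

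Report percent reduction descriptively, for example as the adjusted mean difference divided by the mean baseline PlI. With −1/1 coding, the yes–no difference is twice the coefficient.

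If percent change is kept as primary, at least add baseline PlI to the model and state a rule for zero and near-zero baselines. As shown above, this recovers little power when baselines are low.

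The cost is a documented change of the primary analysis metric in the protocol and the registry. This is more than an editorial note, because percent reduction is named as primary in the abstract and in the methods. The headline effect would be in PlI points. No new data are needed.
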